## Abstract

**Background:**

In people with chronic obstructive pulmonary disease (COPD), limb-muscle dysfunction is one of the most troublesome systemic manifestations of the disease, which at the functional level is evidenced by reduced strength and endurance of limb muscles. Improving limb-muscle function is an important therapeutic goal of COPD management, for which resistance training is recommended. However, current guidelines for resistance training in COPD mainly focus on improving muscle strength which only reflects one aspect of limb-muscle function and does not address the issue of reduced muscle endurance. The latter is of importance considering that the reduction in limb-muscle endurance often is greater than that of muscle weakness, and also, limb-muscle endurance seems to be closer related to walking capacity as well as arm function than to limb-muscle strength within this group of people. Thus, strategies targeting multiple aspects of the decreased muscle function are warranted to increase the possibility for an optimal effect for the individual patient. Periodized resistance training, which represents a planned variation of resistance training variables (i.e., volume, intensity, frequency, etc.), is one strategy that could be used to target limb-muscle strength as well as limb-muscle endurance within the same exercise regimen.

**Methods:**

This is an international, multicenter, randomized controlled trial comparing the effect and feasibility of non-linear periodized resistance training to traditional non-periodized resistance training in people with COPD. Primary outcomes are dynamic limb-muscle strength and endurance. Secondary outcomes include static limb-muscle strength and endurance, functional performance, quality of life, dyspnea, intramuscular adaptations as well as the proportion of responders. Feasibility of the training programs will be assessed and compared on attendance rate, duration, satisfaction, drop-outs as well as occurrence and severity of any adverse events.

**Discussion:**

The proposed trial will provide new knowledge to this research area by investigating and comparing the feasibility and effects of non-linear periodized resistance training compared to traditional non-periodized resistance training. If the former strategy produces larger physiological adaptations than non-periodized resistance training, this project may influence the prescription of resistance training in people with COPD.

**Trial registration:**

ClinicalTrials.gov, ID: NCT03518723. Registered on 13 April 2018.

**Electronic supplementary material:**

The online version of this article (10.1186/s13063-018-3129-y) contains supplementary material, which is available to authorized users.

## Background

Chronic obstructive pulmonary disease (COPD) is currently the fourth leading cause of mortality worldwide and is expected to become the third by 2020. COPD is now considered a multisystem disease, including limb-muscle dysfunction [1]. Limb-muscle dysfunction is considered one of the most troublesome systemic manifestations of the disease and is characterized by limb-muscle atrophy and by a fiber-type shift toward a less oxidative phenotype, which at the functional level is evidenced by reduced strength and endurance [1, 2]. Importantly, this is negatively associated with clinically relevant outcomes such as exercise tolerance [3], functional capacity [4], daily life activity [5], as well as increased health care service use, dyspnea and poor quality of life [6]. Limb-muscle dysfunction is also closely linked to the prognosis of the disease [7]. For example, a mid-thigh muscle cross-sectional area less than 70 cm^2^ is associated with fourfold increase in mortality after adjusting for age, sex and FEV_1_ (1), while each 10% increment of a quadriceps strength (kg) to body mass index (kg/m^2^) ratio is associated to a 9% reduction in mortality [1, 7].

Limb-muscle dysfunction is a heterogeneous process in patients with COPD [8] but this is rarely considered in the exercise training prescription. To date, if the goal is to improve limb-muscle function, a resistance-training strategy is often recommended before other available exercise modalities for people with COPD [9]. For example, larger effects on muscle strength are obtained with resistance training in comparison to whole body aerobic training or when resistance training is added to an aerobic training protocol [9–11]. However, the optimal resistance training prescription for people with COPD with regard to improving either limb-muscle strength or endurance has yet to be determined [9]. Current guidelines for resistance training in COPD [9] mainly focus on improving muscle strength which only reflects one aspect of limb-muscle function and does not address the issue of reduced muscle endurance. This is important because the reduction in limb-muscle endurance is often greater than that of muscle weakness, approximating 32 to 77% in patients with COPD [1, 2]. Limb-muscle endurance also seem to be more closely related to walking capacity as well as arm function than muscle strength in COPD [11, 12]. Thus, improving limb-muscle endurance in patients with COPD should not be neglected in designing resistance training interventions. Furthermore, resistance training performed in accordance to current guidelines also lack a clear structure on how to individualize training schemes. This is of importance as up to 50% of patients with COPD are considered non-responders after exercise training [13–15]. The consensus is that the same training schedules cannot be used for all subjects, even if the goal is the same. Strategies on how to adapt and vary training schemes based on the individual condition, preferably targeting multiple aspects of the decreased muscle function, is warranted to increase the possibility for an optimal effect for the individual patient [16, 17]. This calls for alternative ways of performing resistance training in COPD.

Periodized resistance training, which represents a planned variation of resistance training variables (i.e., volume, intensity, frequency, etc.), is one strategy that could be used to target muscle strength as well as muscle endurance within the same exercise regimen. In healthy adults, periodized resistance training increases muscle strength as well as muscle power significantly more than traditional non-periodized resistance training (RT) [18]. In people with COPD, non-linear periodized aerobic training has resulted in greater effects on exercise capacity as well as quality of life in comparison to traditional aerobic training [17]. However, the potential effect of utilizing the concept of non-linear periodization of training variables during resistance training in people with COPD is less investigated.

Therefore, we intend to perform a trial to investigate the effect and feasibility of non-linear periodized resistance training (NLPRT) compared to traditional RT for people with COPD.

### Primary objective

To compare the effect of NLPRT with RT on isotonic upper (chest press, shoulder flexion) and lower (leg press, calf press) limb-muscle strength and limb-muscle endurance in people with COPD.*Hypothesis*: NLPRT will result in a similar effect size with regard to isotonic leg press, chest press, calf press and shoulder flexion muscle strength but in a larger effect size (> 1.16) with regard to muscle endurance than traditional RT at week 9

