### Secondary objectives

2.To compare the effect of NLPRT and RT on (1) functional performance measured with the endurance shuttle walk test (ESWT), the 60-s Sit to Stand Test (60STS) and the Unsupported Upper Limb Exercise Test (UULEX), (2) isometric quadriceps muscle strength and endurance, (3) health-related, disease-specific quality of life (HRQoL), (4) dyspnea and (5) the proportion of responders for each of these variables (a response being defined as an improvement that is larger than the known minimal detectable change/or minimal important difference for a given variable).*Hypothesis*: NLPRT will result in a greater gain on functional performance, isometric quadriceps muscle endurance, HRQoL dyspnea, as well as a larger number of responders while effects will be similar with regard to isometric muscle strength at week 93.To determine the feasibility of NLPRT compared to RT on attendance rate, duration, satisfaction, drop-outs as well as occurrence and severity of any adverse events.*Hypothesis*: that NLPRT will be feasible to the same extent as RT over 8 weeks of training4.To determine the responsiveness of isometric quadriceps strength and endurance measurement to NLPRT and RT.*Hypothesis*: isometric quadriceps muscle strength measurements will be highly responsive to NLPRT as well as RT represented by a standardized response mean (SRM) > 0.80, while quadriceps endurance measurements will be highly responsive to NLPRT but moderately responsive to RT (SRM 0.50 > 0.80) at week 95.To explore the intramuscular adaptations of NLPRT compared to the intramuscular adaptations of RT*Hypothesis*: NLPRT will result in a larger increase in muscle capillarization as well as in the activity of citrate synthase (CS) and lactate dehydrogenase (LDH) compared to RT at week 9

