### Sample size calculation

Multicenter trials involve a correlation in data, i.e., participants from the same center are likely to be more similar than subjects from other centers. As such, a correlation potentially affects the statistical power of the trial the sample size needs to be adjusted, often increased, to account for the design of the study [21]. To minimize the effect of using different centers, eligibility criteria as well as design and delivery of training interventions are standardized across centers. Furthermore, in an individually randomized trial that is stratified for centers, similar to the present trial, the design effect is estimated to be < 1 which involves a gain in power, allowing a reduction in sample size rather than an increase [21, 22]. Nevertheless, the sample size calculation is performed with a design effect of 1 and is based on the results from a resistance training meta-analysis on healthy adults in which a group difference of 1.16 (SD 1.09) was seen on muscle function when comparing NLPRT with RT [18]. Thus, based on an expected group difference in effect size of 1.16 (SD 1.09) on muscle function with a power of 80%, two-sided alpha of 0.05 (including 15% drop-outs) 16 patients per group is required (32 in total). However, we plan to recruit a total of 64 patients with an equal distribution of men and women. The planned sample size (*n* = 64, including 15% drop-out) will be sufficient to have power for subgroup analysis based on sex (male and female).

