### Statistics

The primary analyses will be an intention-to-treat analysis (including all participants randomized) in addition, a complete case population (participants with complete outcome measurements independent on adherence to intervention), and a per-protocol analysis (defined as at least 80% overall attendance rate as well as no exacerbations during the last 2 weeks prior to follow-up assessment) will be performed. Missing data will be imputed in the intention-to-treat analysis using multiple imputation assuming data is missing at random conditional on participant severity of disease and history of exacerbations. This is because severity of disease and history of exacerbations are known risk factors for future exacerbations and may affect adherence to the training protocol [28].

Mixed models will be used for analysis of data with individuals at level 1 and center at level 2. Estimates of effect sizes will be computed using Cohen’s *d* (*d* = difference in group means/error SD within). Calculated as the difference between predicted means from the final mixed-effects model for a given pair of groups divided by the estimated within-group error SD in the model with the estimated value of $$ 2{\sigma}_e^2 $$, where $$ {\sigma}_e^2 $$ is the residual variance. To judge the quality of the model we will analyze the residuals. For responsiveness, values of 0.20, 0.50 and ≥ 0.80 correspond to small, moderate and large responsiveness, respectively [50].

We will consider two-sided *p* values < 0.05 as statistically significant for the primary outcomes without correction for a multiplicity of tests assuming that each test represents an independent function based on the specificity principle of training [26]. Relationships between parameters will be evaluated using Pearson correlation coefficients. The strength of the correlation coefficients will be categorized as low (0–0.25), moderate (> 0.25–0.50), strong (> 0.50–0.75), very strong (> 0.75). Pre-planned subgroup analyses are differences between men and women. Statistical analysis will be performed using the statistical package SPSS 23.1.

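### The primary hypothesis predicts similar strength gains, but the protocol has only a difference test and no margin by which similarity could be shown

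*Protocol article*

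**What the plan says.** The primary outcomes are 1RM strength and repetitions at 45% of 1RM, each for leg press, shoulder flexion, calf press and chest press. The hypothesis under Primary objective has two halves. For strength, "NLPRT will result in a similar effect size with regard to isotonic leg press, chest press, calf press and shoulder flexion muscle strength". For endurance, it continues "but in a larger effect size (> 1.16) with regard to muscle endurance than traditional RT at week 9".

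The Statistics section sets one rule for both: "We will consider two-sided *p* values < 0.05 as statistically significant for the primary outcomes without correction for a multiplicity of tests". It also says that Cohen's d will be computed from the mixed model. It gives no value of d, and no interval around it, that would count as similar.

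The Sample size calculation rests on an "expected group difference in effect size of 1.16 (SD 1.09) on muscle function with a power of 80%, two-sided alpha of 0.05". With 15% drop-out this gives 16 per group. The trial plans to recruit 64, and the stated reason for the increase is the subgroup analysis by sex.

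No equivalence or non-inferiority margin, and no confidence-interval criterion, appears anywhere in the article.

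**The concern.** A prediction of similarity needs a statement of how large a difference would still be acceptable, and a test that can reject larger ones. Neither is given for the strength outcomes. The only stated criterion bearing on them is whether p falls below 0.05, and a p-value above 0.05 shows only that a difference was not detected. The less precise the trial, the more easily the strength hypothesis would appear confirmed.

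This matters for the comparison being made. The article says that the RT programme primarily aims at strength, and that the last four weeks of the NLPRT programme focus more on endurance. A cost in strength is therefore a real possibility. The Discussion adds that the results may influence how resistance training is prescribed in COPD.

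**Working it through.** **1. What the sample size was built for.** Inputs from the Sample size calculation: difference 1.16, SD 1.09, two-sided alpha 0.05, power 80%, drop-out 15%.

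n per arm = 2 × [1.09 × (1.960 + 0.842) / 1.16]² = 13.86.

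Allowing for drop-out, 13.86 / 0.85 = 16.3 or 13.86 × 1.15 = 15.9. The stated 16 per group is reproduced within rounding as a test of zero difference with 1.16 as the alternative. The arithmetic is not at fault, but nothing in it addresses similarity.

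**2. Evaluable patients.** 64 / 2 = 32 per arm, and 32 × 0.85 = 27.2, so about 27 per arm.

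**3. Precision, unadjusted, in SD units.** The 95% half-width is t(0.975; 52 df) × √(2/27) = 2.007 × 0.272 = 0.546 SD.

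**4. Chance that a real deficit is non-significant.** Noncentral t with 52 df and noncentrality d × √(27/2):

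| True deficit | Noncentrality | P(non-significant) |
|---|---|---|
| 0.3 SD | 1.10 | 81% |
| 0.5 SD | 1.84 | 56% |

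Baseline adjustment multiplies the SD by √(1 − ρ²). For the 0.5 SD deficit the miss rate then falls to about 29% at an assumed ρ = 0.7 and 15% at ρ = 0.8. Precision works the wrong way under this rule. By normal approximation, unadjusted, the 0.5 SD deficit is missed in 55% of trials at 27 per arm and in 75% at 13 per arm.

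**5. What a proper similarity test could deliver.** Two one-sided tests at 5% (90% interval inside the margin), true difference 0, 27 per arm. The documents give neither a margin nor a baseline correlation, so both are assumptions. At a margin of 0.5 SD:

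| Assumed ρ with baseline | Power |
|---|---|
| none (unadjusted) | 14% |
| 0.5 | 35% |
| 0.7 | 63% |
| 0.8 | 83% |

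At ρ = 0.8 a tighter margin lowers this to about 56% (0.4 SD) and roughly 15% (0.3 SD). Without adjustment, by normal approximation, 80% power with 15% drop-out needs a total of about 450 patients at 0.3 SD, 164 at 0.5 SD and 64 at 0.8 SD.

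**6. The 1.16 in the endurance half.** The Primary objective writes 1.16 as a lower bound, and the Sample size calculation writes it as the expected difference. At 27 per arm a test against zero is significant once the observed difference exceeds 1.96 × 1.09 × √(2/27) = 0.58. Its power at a true difference of 1.16 is about 97%. The planned test therefore suits superiority over zero and does not examine a threshold of 1.16.

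**The case against.** The best defence is that the protocol never says a non-significant p-value will be read as similarity. The stated objective is to compare, the hypothesis is phrased in effect sizes, and Cohen's d will be reported. The Discussion makes its practical conclusion depend on NLPRT producing larger adaptations. All of this is correct, and the superiority tests and effect estimates stay valid whatever is done about the wording. But estimating d does not say which values are similar, so the strength half of the hypothesis still has no criterion that could confirm or refute it. A separate analysis plan might hold more detail. A margin, however, defines the hypothesis and drives the sample size, and the article states its hypothesis, test rule and sample size together.

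It is also fair that the planned analysis is intention-to-treat with multiple imputation and mixed models. The 56% and 81% figures are therefore illustrations and not the trial's operating characteristics.

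Three stronger readings are tempting, and the documents do not support them:

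- **That the endurance test is itself wrong.** Powering on an expected effect and testing against zero is standard. The conflict over 1.16 is one of wording.
- **That 1.16 is really an effect on strength.** The Background describes the cited meta-analysis as showing gains in strength and power, but the Sample size calculation attributes 1.16 only to muscle function. The article does not say which outcome produced it.
- **That the secondary and feasibility outcomes share the flaw.** The Secondary objectives do say "while effects will be similar with regard to isometric muscle strength" and expect NLPRT to be as feasible as RT. But the 0.05 rule is stated for the primary outcomes only.

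**Conclusion.** The point holds for the four isotonic strength outcomes. Part of the primary hypothesis is a claim of similarity that the stated rule and sample size cannot support. That conclusion comes from setting the passages side by side and does not depend on any assumed figure.

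Its practical size does depend on assumptions. With about 27 evaluable per arm and no baseline adjustment, differences of around half an SD would often go undetected. Adjustment reduces this, by an amount set by a baseline correlation that the article does not give. Whether 64 patients can show similarity depends on that correlation and on the margin chosen. The wording of the 1.16 threshold is a minor inconsistency.

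**What to change.** Before unblinding, choose one of two routes for the four strength outcomes.

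1. **Keep the similarity claim.** Pre-specify an equivalence or non-inferiority margin and justify it. Conclude similarity for an exercise only if the baseline-adjusted interval for the group difference meets the margin: a 90% interval wholly inside it for equivalence, or a 95% interval excluding a deficit as large as the margin for non-inferiority. Where it does not, report the difference and its interval and state that similarity was not shown.
2. **Withdraw the claim.** Remove the word *similar* from the strength hypothesis and report each difference with its 95% interval.

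In either case, restate the endurance hypothesis as superiority of NLPRT over RT (difference greater than zero), with 1.16 named as the planning value, so that the Primary objective and the Sample size calculation agree.

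The second route costs only wording. The first needs a defensible margin, for which the article offers no 1RM value. With 64 patients it may end with similarity unclaimable for some or all exercises, and a tight margin could call for a much larger trial.

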### Secondary objectives

2.To compare the effect of NLPRT and RT on (1) functional performance measured with the endurance shuttle walk test (ESWT), the 60-s Sit to Stand Test (60STS) and the Unsupported Upper Limb Exercise Test (UULEX), (2) isometric quadriceps muscle strength and endurance, (3) health-related, disease-specific quality of life (HRQoL), (4) dyspnea and (5) the proportion of responders for each of these variables (a response being defined as an improvement that is larger than the known minimal detectable change/or minimal important difference for a given variable).*Hypothesis*: NLPRT will result in a greater gain on functional performance, isometric quadriceps muscle endurance, HRQoL dyspnea, as well as a larger number of responders while effects will be similar with regard to isometric muscle strength at week 93.To determine the feasibility of NLPRT compared to RT on attendance rate, duration, satisfaction, drop-outs as well as occurrence and severity of any adverse events.*Hypothesis*: that NLPRT will be feasible to the same extent as RT over 8 weeks of training4.To determine the responsiveness of isometric quadriceps strength and endurance measurement to NLPRT and RT.*Hypothesis*: isometric quadriceps muscle strength measurements will be highly responsive to NLPRT as well as RT represented by a standardized response mean (SRM) > 0.80, while quadriceps endurance measurements will be highly responsive to NLPRT but moderately responsive to RT (SRM 0.50 > 0.80) at week 95.To explore the intramuscular adaptations of NLPRT compared to the intramuscular adaptations of RT*Hypothesis*: NLPRT will result in a larger increase in muscle capillarization as well as in the activity of citrate synthase (CS) and lactate dehydrogenase (LDH) compared to RT at week 9

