### Randomization and masking

A person not involved with either enrollment, assessments nor training of participants will generate the allocation sequence and assign participants to one of the two interventions.

To prevent foreknowledge of treatment assignment and to keep the allocation sequence concealed from the participants and the researchers, group allocation will be done after the completion of baseline and inclusion tests with a computer random-number generator. Individual randomization, stratified for centers and sex, will be performed with a 1:1 allocation to the intervention and control groups. The allocation sequence will be kept in an opaque, sealed and stapled envelope and will be kept concealed until the end of the outcome assessment. The envelope will be made impermeable to intense light by using aluminum foil inside and sealed using tamper-proof labels.

The outcome assessors will be masked to group allocation. Furthermore, the participants will be given repeated instructions not to reveal their group allocation to the outcome assessors. In case of failure in keeping the outcome assessor masked (i.e., a patient reveals their group allocation), a second trained outcome assessor will be available.

Due to the nature of the intervention neither participants nor instructors of the training sessions will be masked during the intervention, the hypotheses of the trial will, however, not be revealed to the participants before and during the trial. The data analysts will be masked to group allocation.

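### Objective 4 predicts a different responsiveness class in each arm, but about 27 patients per arm cannot separate the classes and no comparison of the two SRMs is stated

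*Protocol article*

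**What the plan says.** Objective 4 (Secondary objectives) concerns how responsive the isometric quadriceps measurements are to each training programme. For strength, it predicts high responsiveness under both programmes, "represented by a standardized response mean (SRM) > 0.80". For endurance, it predicts different classes in the two arms: "quadriceps endurance measurements will be highly responsive to NLPRT but moderately responsive to RT (SRM 0.50 > 0.80".

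The Statistics section adds one sentence on this: "For responsiveness, values of 0.20, 0.50 and ≥ 0.80 correspond to small, moderate and large responsiveness, respectively". Neither section describes a contrast between the two SRMs.

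Objective 2 separately compares isometric quadriceps endurance between the arms and expects the larger gain with NLPRT. The Statistics section provides mixed models for the analysis of data.

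The cut-offs are not written consistently. The range printed for the moderate class, 0.50 > 0.80, is not a valid interval. The upper class begins above 0.80 in objective 4 and at or above 0.80 in Statistics.

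**The concern.** The endurance hypothesis is a statement about a difference between arms, but it is expressed as two within-arm labels. Two estimates on opposite sides of 0.80 can differ by very little, and two estimates in the same class can differ by nearly 0.30. A different label in each arm is therefore not evidence that responsiveness differs.

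Whether this matters in practice depends on how precisely 27 or so patients locate an SRM relative to cut-offs that are 0.30 apart. If the precision is poor, the predicted pattern can appear when the arms are the same and can fail to appear when the hypothesis is true. A statement in the final report that the measurement responds better to one programme than to the other would then rest largely on sampling error.

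**Working it through.** **Inputs from the article.** Planned total 64 ("we plan to recruit a total of 64 patients with an equal distribution of men and women"); 1:1 allocation ("will be performed with a 1:1 allocation to the intervention and control groups"); 15% drop-out (Sample size calculation); class limits 0.50 and 0.80.

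**The plan's own figure.** The stated basis is "an expected group difference in effect size of 1.16 (SD 1.09) on muscle function with a power of 80%, two-sided alpha of 0.05", giving 16 per group with drop-out. The normal approximation gives

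n = 2 × (1.960 + 0.842)² × (1.09/1.16)² = 13.86 per group.

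Multiplied by 1.15 this is 15.9, so 16, which reproduces the stated number. Dividing 14 by 0.85 gives 17, and a t-based calculation gives 15 before drop-out and 18 after. All are within two patients of 16. This calculation concerns the group difference in muscle function. The article gives no precision or error figure for the SRM objective.

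**Evaluable patients.** 64 × 0.85 / 2 = 27.2, about 27 per arm.

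**Precision of one SRM.** With SRM = mean change / SD of change, SE ≈ √(1/n + SRM²/(2n)). For n = 27:

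| True SRM | SE | 1.96 × SE | Approximate 95% range |
|---|---|---|---|
| 0.50 | 0.204 | 0.40 | 0.10 to 0.90 |
| 0.65 | 0.212 | 0.42 | 0.23 to 1.07 |
| 0.80 | 0.221 | 0.43 | 0.37 to 1.23 |

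An estimate in the middle of the moderate class has an interval that covers the whole class and both cut-offs.

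**Chance of the predicted pattern.** With normally distributed changes, the estimated SRM × √n follows a noncentral t distribution with n − 1 degrees of freedom and noncentrality SRM × √n. The arms are independent, so

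P(pattern) = P(NLPRT estimate > 0.80) × P(0.50 ≤ RT estimate < 0.80).

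With the same true SRM in both arms and n = 27:

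| Common SRM | P(high) | P(moderate) | P(pattern) |
|---|---|---|---|
| 0.50 | 0.093 | 0.416 | 3.9% |
| 0.60 | 0.193 | 0.503 | 9.7% |
| 0.65 | 0.261 | 0.514 | 13.4% |
| 0.70 | 0.340 | 0.502 | 17.1% |
| 0.80 | 0.515 | 0.417 | 21.5% |
| 0.90 | 0.687 | 0.289 | 19.9% |
| 1.00 | 0.825 | 0.168 | 13.8% |

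Simulation with 200,000 trials gives 21.3% at 0.80 and 13.5% at 0.65. The reverse pattern is equally likely, so equal arms receive discordant high and moderate labels in about 43% of trials at 0.80 and 27% at 0.65. With no drop-out (32 per arm) the chance of the predicted pattern is 13.3% at 0.65, 22.3% at 0.80 and 12.8% at 1.00, so full retention does not help.

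**If the hypothesis is true.** At 1.00 versus 0.65: 0.825 × 0.514 = 0.42. At 0.90 versus 0.65 it is 35%. Even at 1.50 versus 0.65 it is only 51%, because an RT arm in the exact middle of its class is labelled moderate in about half of trials.

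**What an interval for the difference would look like.** At 1.00 versus 0.65, SE(1.00) = √(1/27 + 1/54) = 0.236. The SE of the difference is then √(0.236² + 0.212²) = 0.317, and the 95% half-width is 0.62 around a difference of 0.35.

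**The case against.** Several points on the other side have weight.

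- **No decision rule is written.** The article states a hypothesis in SRM classes and gives descriptive benchmarks. It does not say that the class of the point estimate confirms or refutes objective 4. This stands. A reader might infer such a rule, but it is an inference, and the percentages above describe what happens if the labels are read against the hypothesis.
- **Intervals may be in an analysis plan that is not shown.** This also stands: the absence of an interval from an article is not itself a fault. The point rests on what the article does state, a between-arm prediction framed as two labels.
- **Objective 4 is about a measurement property.** One SRM per programme is a reasonable summary of that. The endurance hypothesis nevertheless predicts a different class in each arm, which implies a contrast.
- **Objective 2 already compares quadriceps endurance between arms.** A reader might infer that the treatment comparison rests on SRM labels. It does not. But objective 2 concerns the mean gain, while the SRM divides the gain by each arm's own SD of change, so it cannot settle whether the SRMs differ.
- **A flat one-in-five chance would overstate the problem.** That figure holds only for a common SRM of about 0.75 to 0.90, and the article gives no expected value. The percentages also cover only the endurance half of the hypothesis. Requiring strength SRMs above 0.80 in both arms as well cannot raise them.
- **The notation faults are small.** The intended moderate range is clear from the Statistics section, and > versus ≥ matters only at exactly 0.80.

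**Conclusion.** The point holds in a limited form. The only criterion the article gives for objective 4 is the SRM class in each arm, and about 27 patients per arm cannot reliably tell high from moderate. With equal arms the predicted pattern appears by chance in about 4% to 21% of trials over a common SRM of 0.50 to 1.00. With true values of 1.00 and 0.65 it appears in about 42%. The pattern of labels therefore says little either way about a difference in responsiveness.

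The figures assume normally distributed changes, independent arms, no center effect, 15% drop-out spread evenly over the arms, and the usual definition of the SRM. The range of common SRMs is an assumption, shown as a range because the article gives none.

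This is a cheap improvement to a secondary objective. It does not affect the primary outcomes or the comparison of mean gains under objective 2.

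**What to change.** Report each arm's SRM with a bootstrap 95% confidence interval, and report the between-arm difference in SRM with its own bootstrap 95% interval. Base any statement that responsiveness differs between the programmes on the interval for the difference. Keep the class names for description only. Write the classes in the same way in Secondary objectives and in Statistics: moderate as 0.50 to < 0.80, large as ≥ 0.80.

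The change uses data already planned and needs only a short additional analysis. The cost is that the claim becomes harder to make: with a half-width of roughly 0.6, a true difference of 0.35 would usually leave an interval that includes zero.
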